### Study setting

2.4

A total of 240 MAUC patients were recruited by 6 clinical trial centers in China from June 2019 to December 2021. Six clinical trial centers were listed as follows: Jiangsu Provincial Hospital of Chinese Medicine, Peking Union Medical College Hospital of Chinese Academy of Medical Sciences, Guangdong Provincial Hospital of Chinese Medicine, Chongqing Traditional Chinese Medicine Hospital, The Second Affiliated Hospital of Fujian Traditional Chinese Medicine University, and Shaanxi Traditional Chinese Medicine Hospital. The inclusion of the case complies with the principle of geographical balance nationwide. Internal physicians will screen eligible patients from outpatient clinics. Before the enrollment, all patients will receive a comprehensive view of informed consent, including objective, interventions, scheduling, the benefits and risks of this trial. An informed consent form is mandatory for enrollment.

### Eligibility criteria

2.5

Diagnostic criteria:

1.The western medicine diagnostic criteria of UC will refer to Chinese consensus on diagnosis and treatment of IBD (Beijing, 2018).^[14]^2.The TCM diagnostic criteria of the damp-heat stasis blocking and spleen-qi deficiency syndrome will refer to the Clinic terminology of traditional Chinese medical diagnosis and Consensus of traditional Chinese medical in diagnosis and treatment of UC.^[15,16]^ Diagnosis of this syndrome including the main and minor symptoms as following:

Main symptoms:

1.Diarrhea, mucus and bloody stools;2.Abdominal pain;3.Tesmus;4.Tired and lazy;

Minor symptoms:

1.burning anus;2.short and dark-color urine;3.dry and bitter in the mouth;4.drowsiness of limbs;5.poor appetite.

Tongue and pulse: red tongue, thick yellow fur with tooth marks on the sides, and smooth pulse.

Confirmation of the syndrome type: 2 main symptoms (required for the first item) plus 2 minor symptoms, which can be diagnosed by referring to the tongue and pulse.

Inclusion criteria:

1.Diagnosed with active UC.2.Defined by modified Mayo score of 3 to 5 points (mild period).^[14]^3.Differentiation of TCM syndrome is damp-heat stasis blocking accompanied with spleen-qi deficiency.4.Age >18 and <65 years.5.Voluntary to participate and providing written informed consents, as required by Good Clinical Practice.

Exclusion criteria:

1.Patients during remission period, moderate or severe period.2.Pregnancy, lactation, or have desire for pregnancy.3.Severe allergy or allergic to mesalazine or any of the ingredients in HEC.4.Have cardiovascular, pulmonary, liver, renal, endocrine, nerve, and hematology diseases. Blood creatinine level, blood alanine transaminase or aspartate aminotransferase level above the upper limit of normal.5.Have serious complications, such as intestinal stenosis, intestinal obstruction, intestinal perforation, multiple intestinal polyps, toxic megacolon or colorectal cancer, etc.6.Mental disorders or other causes which result in inability of proper expression of feelings.7.Have participated in other medical clinical studies in the last 3 months.8.In addition to mesalazine, receiving other treatments for UC.9.Serious and unstable condition requiring emergency treatment.10.Inappropriate to participate in this trial judged by clinical physicians.

Termination and withdrawal criteria:

1.The participant is not willing to continue the clinical trial.2.No medication or any follow-up records;3.Important deviations occur in the process of the clinical trial, such as poor compliance.4.Occurrence of allergic reactions or serious adverse events during the trial.5.Not alleviated or the symptoms are aggravated.

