Numerous studies based on UC mouse models and clinical trials, especially randomized double-blinding clinical trials, remains the gold standard for evaluating the efficacy of TCM.^[9]^ To obtain more conclusive results on the risk-benefit ratio of TCM for UC, it is necessary to design and conduct a high-quality clinical trial with appropriate blinding method and a large number of patients. Hudi enteric-coated capsules (HEC) has finished a multi-center clinic randomized controlled trial in China,^[10]^ it confirmed that HEC played a pivotal role in treating mild to moderate UC by relieving symptoms effectively, but as the shortage of colonoscopy examination and treatment time, this trial was not rigorous enough. Besides, the mechanism of HEC in treating UC was not clear.

Therefore, the primary aim of this multi-center, double-blinding, double-dummy, randomized controlled trial is to evaluate the clinical efficacy and safety of HEC in the treatment of mild active UC patients. Meanwhile, we want to reveal the underlying mechanism of HEC how to treat mild active UC by molecular biology technology from the clinic specimens.

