### Outcomes

3.4

Primary therapeutic outcome: the rate of clinical efficacy and clinical remission at 8 weeks of treatment (last survey point) according to the modified Mayo score (Table 2). Clinical efficacy was defined as a decrease of at least 30% from the baseline and a decrease ≥3 points, with an accompanying decrease in the subscore for bloody stools ≥1 point or absolute bloody stools subscore of 0 to 1. Clinical efficacy rate = effective number / total number of the group ×100%. Clinical remission was defined as a score ≤2, with no individual subscore with a value greater than 1. Clinical remission rate = remission number / total number of the group ×100%.

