## Discussion

4

Compared with UC in Western countries, UC in China has some differences in clinical characteristics. And the prevalence and incidence rates of UC in China were increased rapidly.^[19]^ It is of great significance to find Chinese medicine preparations for the treatment of UC to supplement the selection of clinical drugs. UC is a chronic IBD characterized by a relapsing-remitting course owing to recurrent intestinal inflammation. If the disease can be effectively controlled during mild to moderate period, which will greatly reduce the patient's pain and anxiety. In a clinical randomized controlled trial of HEC in the treatment of active UC, we found the efficacy of TCM syndromes of HEC group was 91.09%, and the positive control group (Mesalazine) was 84.62% after 6 weeks of treatment. HEC was effective in improving the symptoms of patients with mild to moderate UC.^[10]^ The shortcomings of the study were the short study time, lack of enteroscopy, and the Mayo score cannot be used as the primary therapeutic outcome. Therefore, this study extended the treatment time to 8 weeks, completed colonoscopy and intestinal mucosa biopsy, and evaluated the efficacy from the modified Mayo score before and after treatment. The results from this study may provide evidence-based clinical evidence on the effectiveness, safety, and reduce or substitute mesalazine of HEC.

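### The entry criteria state no minimum endoscopy subscore, so a patient with endoscopy 0 can enter as active UC and, from a baseline total of exactly 3, meet clinical remission on a one-point symptom fall

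*Protocol article*

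**What the plan says.** Section 2.5 (Eligibility criteria) combines several entry conditions:

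- Inclusion 1: "Diagnosed with active UC". On the diagnosis itself, "The western medicine diagnostic criteria of UC will refer to Chinese consensus on diagnosis and treatment of IBD (Beijing, 2018".
- Inclusion 2: "Defined by modified Mayo score of 3 to 5 points (mild period".
- Inclusion 3: the TCM syndrome, confirmed by "2 main symptoms (required for the first item) plus 2 minor symptoms". The first main symptom covers diarrhea with mucus and blood.
- Exclusion 1: "Patients during remission period, moderate or severe period".

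None of these states a minimum endoscopy subscore.

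In section 3.4 (Outcomes) the primary outcome has two parts. For remission, "Clinical remission was defined as a score ≤2, with no individual subscore with a value greater than 1", with no minimum fall from baseline. Clinical efficacy needs a fall of at least 3 points and at least 30%, plus a bloody-stool condition. The same section shows that endoscopy is a component of the score: endoscopic response is a fall of at least 1 point in it, and mucosal healing is a value of 0 or 1.

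Section 2.2 declares a noninferiority design against mesalazine, with no placebo-only arm.

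**The concern.** The Introduction criticises the previous HEC trial: "as the shortage of colonoscopy examination and treatment time, this trial was not rigorous enough". The Discussion presents the new trial as the remedy, having "completed colonoscopy and intestinal mucosa biopsy, and evaluated the efficacy from the modified Mayo score before and after treatment". Yet the stated entry rule uses the endoscopy subscore only as one addend in a total. Symptom items alone can supply 3 to 5 points, so the total does not establish that the mucosa is inflamed.

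Two consequences follow. First, patients whose symptoms do not come from mucosal inflammation may well respond at similar rates on either drug. That pulls the arms together, and without a placebo arm the trial cannot tell this apart from two equally effective drugs. Second, a patient who starts at endoscopy 0 cannot achieve endoscopic response, yet counts as mucosal healing at week 8 unless the subscore rises to 2 or more. Both rates use the whole group as denominator.

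**Working it through.** **Inputs.** Entry total 3-5 (2.5); remission total ≤2 with no subscore above 1, and efficacy as a fall of ≥3 points and ≥30% plus the bloody-stool condition (3.4); planning rates 83.11% and 68% (2.3). Table 2 is not shown, so I assume four items scored 0-3: stool frequency, bleeding, endoscopy, global assessment. A three-item version without the global assessment is the check.

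**Step 1: do the stated criteria admit endoscopy 0?** Take stool frequency 1, bleeding 1, endoscopy 0, global assessment 1.
- The total is 1+1+0+1 = 3, within 3-5.
- Bleeding and stool frequency are both above 0, so the pattern is compatible with the mandatory first main symptom.
- The only remission definition in the document needs a total ≤2. A total of 3 is not remission by that rule, so exclusion 1 does not remove the patient.

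**Step 2: how many patterns?**

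| Four items scored 0-3 | Total 3 | Total 4 | Total 5 | Sum |
|---|---|---|---|---|
| All patterns | 20 | 31 | 40 | 91 |
| Endoscopy 0 | 10 | 12 | 12 | 34 |
| Endoscopy 0 and bleeding 0 | 4 | 3 | 2 | 9 |

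By symmetry 34 patterns have bleeding 0. If bleeding ≥1 is required, 91 - 34 = 57 patterns remain, of which 34 - 9 = 25 have endoscopy 0. In the three-item version 9 of 34 patterns have endoscopy 0.

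**Step 3: the one-point route.** A one-point fall reaches a total ≤2 only from 3; totals of 4 and 5 need falls of 2 and 3. The Step 1 patient drops to 2 with every subscore ≤1 and is in remission. Of the four-item patterns, 13 reach remission by a one-point fall in a non-endoscopic item: 7 with endoscopy 0 (5 of them with bleeding ≥1) and 6 with endoscopy 1. In the three-item version there are 5, split 2 and 3.

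**Step 4: clinical efficacy.** From a total of 3, a fall of 3 means reaching 0. No one-point change qualifies.

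**Step 5: dilution.** Let d be the true difference in patients with endoscopy ≥1 and f the share with endoscopy 0 who respond alike in both arms. Then

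observed difference = (1-f) × d + f × 0 = (1-f)d.

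The plan gives no figure for f. The values below are assumptions.

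| f | HEC truly 15 points worse | Planned difference, 83.11 - 68 = 15.11 |
|---|---|---|
| 10% | 13.5 | 13.6 |
| 20% | 12.0 | 12.1 |
| 30% | 10.5 | 10.6 |

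The first column is the one that matters for a false noninferiority claim. The second shows the same shrinkage of the advantage used in planning. Step 5 does not depend on the one-point route.

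**The case against.** Several stronger readings are tempting, and the documents do not support them.

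- *Entry rests on the total score alone.* It does not: diagnosed active UC and the TCM syndrome are required, and remission is excluded. The cited consensus may itself demand endoscopic activity, and so may the full protocol; neither can be checked here. For the same reason one cannot claim that colonoscopy plays no part in confirming active disease. What stands is that the article gives its own operational definition of mild activity, as a total, and sets no endoscopic floor.
- *A patient without bleeding shows the problem.* On its natural reading the mandatory first main symptom excludes that patient. The example must include bleeding, and blood and mucus in the stool make a wholly non-inflammatory picture less likely. They are still symptoms, not endoscopic confirmation.
- *One-point remission is a general route to primary success.* It exists only from a baseline total of 3, and only for remission. The sample size in section 2.3 is built on efficacy rates, which this route does not touch.
- *An endoscopic minimum closes the route.* It does not: 6 of the 13 one-point patterns have endoscopy 1. The route comes from the small gap between entry at 3 and remission at 2. A subscore of 1 also already counts as mucosal healing.
- *34 of 91 is a share of patients.* It is a count of possible patterns. Nothing in the documents supports a particular f, an equal response in both arms, or a 15-point HEC deficit.

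On the other side, exclusion 8 bars UC treatments other than mesalazine and so reads as admitting patients already taking it. Residual symptoms over a quiet mucosa are plausible in that group.

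**Conclusion.** The point holds in a limited form. As written, the entry criteria admit a patient with endoscopy 0, and nothing shown in the document closes that gap. For such a patient endoscopic response is impossible, and from a total of 3 remission is one symptom point away.

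The effect on the noninferiority comparison has a known form, (1-f)d, and a known direction when HEC is truly worse. Its size is unknown, because f is not given. The text shown also states no margin, so the added risk of a false noninferiority conclusion cannot be quantified. The pattern counts rest on the assumed item list and 0-3 scoring, but the gap appears in both the four-item and three-item versions. This is a cheap improvement worth making, not a flaw that invalidates the design.

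**What to change.** Add to inclusion 2, after the total of 3 to 5: *with an endoscopy subscore of at least 1 at the baseline colonoscopy*. The subscore is already needed to compute the total, so the cost is one clause and a few more screen failures. The sample size formula is unaffected.

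Section 2.4 gives recruitment from June 2019 to December 2021. If enrolment is under way, prespecify instead, before unblinding, the primary comparison restricted to patients with a baseline endoscopy subscore of at least 1 as a sensitivity analysis. That costs one added analysis. If the cited consensus or the full protocol already requires endoscopic activity for active UC, stating the threshold in the eligibility section is enough.

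Either change secures or examines endoscopic inflammation at entry. Neither removes every one-point route to remission.

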### Trial design

2.2

This study is a multi-center, double-blind, double-dummy, randomized, parallel positive controlled trial. We adopted a noninferiority trial design and followed the Standardized Protocol Interventions: Recommendations for Interventional Trials (SPIRIT) 2013 Statement.^[11]^ The experimental group was treated with HEC and enteric-coated mesalazine tablets (EMT) placebo, while HEC placebo and EMT were used in the control group. A total of 240 patients diagnosed with mild active ulcerative colitis (MAUC) and TCM syndrome of damp-heat stasis blocking and spleen-qi deficiency in 6 clinical trial centers are eligible for enrolment. We will implement randomization with a 1:1 allocation ratio in the experimental group (n = 120) or the control group (n = 120), and each patient will undergo an 8-week treatment. The study flowchart is showed in Figure 1.

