### Number of Samples

2.3

Number of Samples was determined based on the calculation of noninferiority trial design. The efficacy rates of EMT ranges from 65% to 71%,^[12,13]^ and the average rate is about 68%. Our previous study found that the efficacy rates of HEC is 83.11% in treating MAUC. The sample size was calculated by the following formula: 

*U*α, *U*β is the corresponding *U* value of α, β. When α equaling to 0.05, β equaling to 0.1, *U*α (0.05) is 1.645, *U*β (0.2) is 0.842. *P*_1_ and *P*_2_ represent the efficacy rates of HEC and EMT. *P* equals to (*P*_1_ + *P*_2_) /2 × 100%. The certainty was set at 80%, considering 20% of sample lose. The sample number was set to 120 for each group, 240 in total, and 40 samples in each center.

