### Research personnel

2.7

Experienced physicians will be responsible for recruiting and evaluating the participates in this trial. Postgraduates in gastroenterology will be trained by the principal investigator before participating in this trial. They will dispatch drugs, fill in case report forms (CRFs), and record detailed reasons for the patient's withdrawal from the trial.

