### Intervention plan

3.2

Both 2 groups will be treated with drugs for 8 weeks continuously, and the administration method of drugs has been designed as described in Table 1.

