### Follow-up

3.3

Each patient was provided with a participant diary card to record diary signs and symptoms of diarrhea, mucilage or blood–pus stools, abdominal pain, and tenesmus. Patients will be interviewed every 2 weeks after enrollment in the trial, while they should return the remaining drugs and packages, and receive the drugs they need to take for the next 2 weeks. Assessment of study endpoints and duration of follow-up was shown in Figure 2.

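### Lack of improvement alone, with no earliest time and no need for other treatment, is a withdrawal ground, so slow responders can be taken out before the week-8 primary assessment

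*Protocol article*

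**What the plan says.** All references are to the protocol article.

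- **Section 2.5, Eligibility criteria (termination and withdrawal list), item 5:** "Not alleviated or the symptoms are aggravated". The two halves are joined by *or*, so lack of improvement is enough without worsening. No week, score, degree or need for rescue treatment is attached.
- **Section 2.7, Research personnel:** trained postgraduates are to "record detailed reasons for the patient's withdrawal from the trial". The wording is about leaving the trial, not about stopping study drug.
- **Section 3.2, Intervention plan:** "Both 2 groups will be treated with drugs for 8 weeks continuously".
- **Section 3.3, Follow-up:** "Patients will be interviewed every 2 weeks after enrollment in the trial".
- **Section 3.4, Outcomes:** the primary outcome is "the rate of clinical efficacy and clinical remission at 8 weeks of treatment (last survey point"), scored on the modified Mayo score. The response rate is given as "Clinical efficacy rate = effective number / total number of the group", and the remission rate is built the same way.
- **Section 2.2, Trial design:** "We adopted a noninferiority trial design".

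**The concern.** The primary endpoint asks whether a patient has improved enough by week 8. Item 5 allows a patient to be withdrawn because improvement has not yet come. Whether the week-8 result is ever observed then depends on the early course of the same outcome.

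Withdrawing a patient who worsens is ordinary protection and is not questioned here. The difficulty is the patient who is stable, needs no other treatment and might respond in the second half of the treatment period. Under item 5 that patient can be taken out at the first visit after baseline, and six centres have no stated rule for choosing when to do so.

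What is at stake is limited. If withdrawn patients stay in the denominator, they count as not effective. The loss is then confined to those who would have responded by week 8 had they continued. If the two arms differ in how many such patients they have, the difference used for the noninferiority comparison moves. An analysis plan can decide how to classify a withdrawn patient, but it cannot recover a week-8 assessment that was never made.

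**Working it through.** **1. When the rule can act.** Two-weekly visits before week 8 fall at weeks 2, 4 and 6, so there are three occasions before the primary assessment.

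**2. How the sections fit together.** Section 3.2 foresees eight weeks of uninterrupted treatment, and section 3.4 places the primary assessment at the end of them. Section 3.4 also grades the TCM syndrome score at weeks 2, 4 and 8, with categories for a fall of less than 30% and for worsening, so it expects some non-improved patients to be followed. Item 5 lets those same patients be withdrawn at week 2. Nothing shown limits item 5 to study drug or states that withdrawn patients return at week 8.

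**3. Inputs for a size.** The plan gives no figure on this point to reproduce. Two of its inputs are used:
- 120 patients per arm (section 2.3). This can be reproduced from the section's rates and quantiles: mean rate (0.8311 + 0.68)/2 = 0.7556; 2 × 0.7556 × 0.2444 × (1.645 + 0.842)² / (0.8311 − 0.68)² ≈ 100.1; times 1.2 for loss ≈ 120.
- A mesalazine rate for which "the average rate is about 68" per cent is stated (section 2.3).

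Two further inputs are needed and are not in the documents: *s*, the share of an arm stopped under item 5, and *r*, the share of those who would have responded by week 8. Both are assumed below.

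**4. Formula.** With all patients in the denominator and stopped patients counted as not effective, an arm's rate falls by s × r. The difference HEC minus mesalazine therefore shifts by

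s(mesalazine) × r(mesalazine) − s(HEC) × r(HEC).

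Each stopped patient who would have responded costs the arm 1/120 = 0.83 percentage points.

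**5. Results.**

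| Assumption | Shift in the difference |
|---|---|
| Equal s and equal r in both arms | 0 |
| r = 0 in both arms | 0 |
| s = 5% HEC, 10% mesalazine; r = 20% in both | 0.10 × 0.20 − 0.05 × 0.20 = +1.0 point (1.2 of 120 patients) |
| s = 5% HEC, 10% mesalazine; r = 40% in both | 0.10 × 0.40 − 0.05 × 0.40 = +2.0 points (2.4 of 120 patients) |
| s = 10% HEC, 5% mesalazine; r = 40% in both | −2.0 points |

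A positive shift favours HEC and a negative one counts against it. The documents do not say which is likelier.

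**6. Scale.** With 68% in both arms and 120 per arm, the standard error of the difference is √(2 × 0.68 × 0.32 / 120) = 0.0602, or 6.0 points. The largest illustrated shift is 0.020 / 0.0602 = 0.33 of a standard error.

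**The case against.** The strongest reply has four parts.

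*The article is condensed.* A full protocol dated April 2019 exists and is not shown. It may define the timing, the degree and the procedures after withdrawal. The schedule figure is also missing, so an assessment at termination cannot be ruled out. This stands as a caution, and nothing is claimed here about Mayo scores taken before week 8. It does not remove the point, because the stated rule, followed literally, allows early withdrawal for mere lack of response.

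*Leaving the trial is partly inferred.* The heading of the list does not say which items stop treatment and which end participation. Section 2.7 is a staffing sentence and does not define item 5. This also stands. It is a further reason to settle the wording.

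*Safeguards exist.* Participants and investigators are blinded, reasons for withdrawal are recorded, and the sample size allows for 20% loss. Blinding should make the rule be applied alike in both arms, but it does not make the number of patients who meet it alike. That number depends on how fast and how well each drug works.

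*Counting stopped patients as failures changes nothing.* If the total-group denominator already counts them as not effective, repeating this in the fix gives the same primary rate. That is correct. The gain comes from the other two changes: fewer slow responders are stopped, and week-8 data exist for those who are.

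A reader might infer something stronger: that withdrawn non-responders leave the denominator, so both rates rise and a true deficit shrinks in favour of noninferiority. For example, with assumed true rates of 58% and 68% and half of the non-responders removed from each arm, the difference would move from −10.0 to −7.5 points. The documents do not support this reading. Section 3.4 divides by the total number of the group and nowhere says that withdrawn patients are removed from it. If all randomised patients stay in, there is no such shift.

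**Conclusion.** The point holds as a defect in a stated rule. Item 5 makes lack of improvement alone a termination or withdrawal ground, without an earliest time or a need for other treatment. As written, it can take out a patient who has not yet responded at week 2, 4 or 6, before the assessment on which both primary rates rest.

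The consequence is modest and cannot be quantified from the documents. The between-arm bias is zero if stopping and late response are equal in the arms, or if no stopped patient would have responded. Otherwise it can go either way. The illustrated 0 to 2.0 points in size rests wholly on assumed stopping and late-response shares, and on stopped patients being counted as not effective. The documents do not support a claim that the trial's conclusion would change, and none is made. The change is worth making because it is cheap and keeps data that cannot be recovered later.

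**What to change.** 1. Reword item 5 as a ground for stopping study drug, not for leaving the trial. It should apply to clinically significant worsening, or to lack of improvement that in the physician's judgement needs other treatment. Slow responders who need no rescue can then complete 8 weeks, and nobody who needs other treatment is held on study drug.
2. Keep every stopped patient who still consents on the week-8 assessment already scheduled. Record the stop date and any rescue treatment.
3. State that all randomised patients stay in the denominator and that stopping for lack of effect, or rescue, counts as non-response. If the total-group rate in section 3.4 is read this way already, this confirms the primary rate and does not change it.
4. Report the observed week-8 results, including those of stopped patients, as a sensitivity analysis.

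The cost is a change of protocol wording and an instruction to the six centres; no visit is added. The downside is that some stopped patients will decline the week-8 endoscopy or will have started other treatment, so the sensitivity data will be incomplete. If enrolment has already advanced, item 3 can still be applied to everyone, and items 1 and 2 to patients still in the trial.
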